## Methods

The INTEGRATED study is a before and after feasibility study within the ‘health services’ research domain with the aim of trialling a new model of care intended for use in a larger cluster randomised controlled trial (RCT). The protocol has followed the TIDieR (Template for Intervention Description and Replication framework) Framework. The study is being conducted in metropolitan Sydney, Australia, and commenced recruitment in October 2018 with the aim of continuing to review participants into June 2020. The research and data collection plan is summarised in Fig. 1. A minimum of four general practices will be recruited to the study from a local Primary Health Network (PHN). Physiotherapists from the rehabilitation service of the corresponding Local Health District (LHD) will run a weekly respiratory clinic at each of the participating general practices.

**Fig. 1 Fig1:**
[figure not shown]
Study and data collection processes

### Inclusion criteria

#### General practices

General practices will be eligible if they use computerised clinical software, have a room available for use by the physiotherapist and are interested in an integrated GP-physiotherapist partnership model for COPD management. Where possible, general practices will be chosen that meet the PHN strategic directions for integrated care and are close to one of the PR programmes provided by the LHD.

#### Patients

The INTEGRATED study will target two groups of patients—new cases of COPD and those with existing COPD. The inclusion criteria have been successfully used in a previous primary care COPD case-finding study [12].

#### New cases of COPD

Patients will be eligible if they have attended the practice at least twice with one visit in the preceding 12 months, are aged 40 years or over and have a documented history of smoking (current or former smoker) in their medical notes. A history of current smoking or past smoking will identify those patients who are at high risk of developing COPD.

#### Existing COPD

Patients will be eligible if they are aged 40 years or over, have a recorded diagnosis of COPD or are taking medications prescribed for COPD (such as short-acting inhaled β_2_ agonists (SABA), short-acting muscarinic antagonists (SAMA), long-acting inhaled β_2_ agonists (LABA), long-acting muscarinic antagonists (LAMA), combination of LABA/LAMA and inhaled corticosteroids), and they have visited the practice in the last 12 months.

Patients will be excluded if they have terminal cancer, cognitive impairment, require home oxygen, do not speak sufficient English or are pregnant.

### Recruitment

#### General practice and physiotherapist recruitment

Recruitment will be conducted with assistance from the PHN. An expression of interest will be included in the newsletter sent to local practices. Those practices expressing an interest in taking part in the study will be visited by an investigator to discuss the study and answer any questions. The practices will be provided with an information sheet and asked to provide written consent to participate in the study. As requested by the local ethics committee, a contract will be prepared and signed between the LHD and the general practices taking part in the study. This will be forwarded to the ethics committee before the practice starts the study. The LHD will identify a senior respiratory physiotherapist with at least 5 years of clinical experience in the management of chronic respiratory conditions to partner with each of the participating general practices. These physiotherapists are experienced senior clinicians who have specialist knowledge within their discipline [34] and have undergone extensive training to develop their skill set for chronic respiratory disease management. They will have high-level skills in spirometry including interpretation, COPD management and self-management, exercise prescription and physical activity advice.

#### Training of physiotherapists

All physiotherapists will receive training in case-finding for the diagnosis of COPD. This will comprise two workshops. This first workshop will cover the case-finding approach for the diagnosis of COPD with performance of spirometry based on the European Respiratory Society (ERS)/American Thoracic Society (ATS) quality criteria and its interpretation [35] as this is essential to the accurate diagnosis and assessment of COPD [5]. The second workshop will include training on COPD management such as smoking cessation advice and referral, physical activity advice and referral to pulmonary rehabilitation if required, preparation of a care plan with the general practice team and the processes for the case-finding and follow-up appointments.

#### Patient recruitment

Potentially eligible patients will be identified from a search of the practice electronic records of all participating general practices by either a research assistant or trained practice staff. The resultant list will be checked for exclusions by the GPs and /or PNs. All potentially eligible patients will be sent an invitation from the practice inviting them to take part in the study. Those interested in the study will be asked to return the completed form in a pre-paid envelope and to also provide written informed consent.

#### Patient and public involvement statement

Patient input was obtained from the qualitative feedback of the PELICAN study [12] and was used to refine the model of care to determine the added value of the physiotherapist to the primary care team. It was not possible to involve patients in the study design beyond this. The qualitative feedback from the participants in this pilot study will be used to further modify the intervention for a larger study. We had health service involvement in the setting of the study aims from the rehabilitation service in the LHD. They were directly involved in establishing the project around the priorities for their chronic disease integration service which aimed to engage with a less severe patient population in primary care who would benefit from pulmonary rehabilitation.

### Study processes

#### Baseline assessment

All patients (new cases and existing COPD) will be required to complete the following questionnaires at baseline: demographic questionnaire, COPD Diagnostic Questionnaire (CDQ) [36], COPD Assessment Test (CAT) [37], Modified Medical Research Council Dyspnoea Scale (mMRC) [38], Patient Activation Measure (PAM) [39, 40], Physical Activity Stages of Change Questionnaire (PASOCQ) [41] and Active Australia Questionnaire (AAQ) [42]. All patients will undergo pre- and post-bronchodilator spirometry based on the ERS/ATS lung function guidelines [35]. The physiotherapist will then determine the level of obstruction for those with existing COPD or determine whether the patient has a diagnosis of COPD which will be based on post-bronchodilator results of a forced expiratory volume in one second (FEV_1_)/forced vital capacity (FVC) < 0.7. Patients will be included for follow-up testing in the study based on a COPD diagnosis from spirometry testing determined by the physiotherapist. If spirometry appears abnormal for other reasons, the results will be discussed with the GP and where appropriate patients will be referred for further testing with respiratory specialists.

### Intervention

The intervention will be coordinated by the physiotherapist at each site under the supervision of the general practice staff. Participants will be free to decline or discontinue any or all of the intervention components at any point in time.

#### New cases of COPD

The physiotherapist will initiate and work in partnership with the GP and patient to develop a COPD specific GP Management Plan (GPMP) and where necessary, Team Care Arrangement (TCA) [43] for the participant using the template developed from the PELICAN Study [44]. This is necessary in Australia to access Medicare subsidised management by an allied health provider such as a physiotherapist. The problems identified in the assessment and the plan of action including details of specific management will be documented. If necessary, patients will also be referred back to the GP for review and medical management as required. Patients will receive physical activity advice and counselling using the 5 A’s approach (Ask, Advise, Assess, Assist, Arrange follow-up) according to the Australian Physical Activity and Sedentary Behaviour Guidelines [45] and a pedometer to monitor their physical activity goals and guide exercise prescription at follow-up appointments. The 5As are a clinical tool recommended for health behaviour counselling in primary care which will enable the physiotherapist to identify barriers to engaging in regular physical activity as well as strategies to overcome these barriers and tailor physical activity goals towards the participant. Patients will also be referred to PR if they meet the requirement according to the COPD-X guidelines [5]. These guidelines state that all patients with COPD (of all mMRC grades) will benefit from PR and recommend that all patients with exertional dyspnoea, those at risk of exacerbation and following an exacerbation should be referred to PR [5]. All current smokers will receive individualised smoking cessation advice and support and appropriate referrals will be made back to the GP as informed by the Royal Australian College of General Practitioners (RACGP) guidelines [46]. Participant education booklets regarding physical activity guidelines, smoking cessation and COPD management will also be provided.

#### Existing COPD

As for new cases of COPD, the physiotherapist will review the current GPMP and TCA or develop one in partnership with the GP if there is no existing GPMP/TCA. Patients with existing COPD will also receive physical activity advice and counselling using the 5 A’s approach, a pedometer and smoking cessation advice and referral if applicable. Patients will also be referred to PR if they meet the requirement according to the COPD-X guidelines [5] and receive participant education booklets regarding physical activity guidelines, smoking cessation and COPD management.

#### Those without COPD on spirometry

Physical activity advice and counselling using the 5 A’s approach will be provided according to the Australian Physical Activity and Sedentary Behaviour Guidelines [45]. All current smokers will receive individualised smoking cessation advice and support and appropriate referrals will be made back to the GP. These patients will not return for further follow-up with the physiotherapist.

#### Follow-up assessment

All participants with existing or newly diagnosed COPD will return for a follow-up visit with the physiotherapist at 1 month to review current physical activity levels and establish a physical activity goal to progress towards at 3 months. A final assessment will be conducted at 3 months to review physical activity goals and complete questionnaires.

### Outcome measures

The physiotherapist will collect demographic information including age, gender, body mass index, employment status, education and country of birth for all individuals who attend the respiratory clinic. Patient and process outcomes will also be collected in people with existing COPD and those with newly diagnosed COPD.

Data will be collected at baseline and at the 1-month and 3-month follow-up visits so the level of change in the outcomes following the intervention can be determined. If patients are unable to attend the appointment at 3 months with the physiotherapist, the research assistant will complete the assessment by telephone.

#### Primary outcomes

##### Feasibility outcomes

A summary of the outcomes that will be used to determine the feasibility of this health service model on the effective identification and management of COPD can be found in Table 1. The primary outcome measures will be number (%) identified with obstruction from the case-finding cohort and number (%) eligible and referred to PR programmes. The success target for number (%) identified with obstruction will be set at 15% as previous studies have reported rates of case finding new diagnoses of COPD between 4 and 27% [12–14]. International literature suggests that only 5% of eligible patients are referred by GPs to PR [20]. We would determine the clinics successful if 80% of eligible participants are referred to PR by the clinics and at least 50% of those referred attend an appointment.

**Table 1 Tab1:** Summary of process outcomes to determine feasibility

Existing COPD	New cases of COPD
Number (%) with spirometry completed (FEV_1_ and FVC data) meeting ERS/ATS quality criteria	Number (%) with spirometry completed (FEV_1_ and FVC data) meeting ERS/ATS quality criteria
Number of known COPD patients over 40 years in the general practice	Number of smokers/ex-smokers over 40 years in the general practice
Number (%) invited to attend	Number (%) invited to attend
Number (%) attended first appointment with physiotherapist	Number (%) attended first appointment with physiotherapist
Number (%) confirmed diagnosis and severity	Number (%) confirmed diagnosis and severity
Number (%) eligible for PR	Number (%) eligible for PR
Number (%) referred to PR	Number (%) referred to PR
Number (%) attended PR	Number (%) attended PR

##### Acceptability of the partnership approach

All the participating GPs and physiotherapists will be asked to take part in one semi-structured interview to explore their experiences of providing an integrated model of care for COPD. There will be at least four GPs and four physiotherapists interviewed. A sample of patients (*n* = 20) will also be asked to take part in semi-structured interviews to examine their experience of being involved in the INTEGRATED study. Themes explored will include satisfaction with the programme and the effects and value of physiotherapist input into COPD diagnosis and management. Barriers and facilitators to the integrated management approach, as well as to access and uptake of evidence-based interventions such as PR, will also be examined. GPs and physiotherapists will be asked to reflect on their roles in the project and how they worked together to manage people with COPD. Physiotherapists will also be asked to reflect on their skill set and how their skill set prepared them to be integrated into the general practice team. All interviews will be digitally recorded and transcribed verbatim in preparation for thematic analysis.

##### Secondary outcomes

The secondary outcome measures are summarised in Table 2 and consist of the patient-relevant outcomes. Health status and symptom score will be measured by the CAT. The CAT has been shown to be a validated tool in the assessment of disease-related quality of life [37] with the most reliable estimate of the minimum important difference being a change of 2 points [47]. Dyspnoea will be assessed using the mMRC [38] which is rated on a scale of 0 (‘I only get breathless with strenuous exercise’) to 4 (‘I am too breathless to leave the house’ or ‘I am breathless when dressing or undressing’).

**Table 2 Tab2:** Summary of patient outcomes

Existing COPD	New cases of COPD
Symptom Score (CAT)	Symptom Score (CAT)
Meeting physical activity guidelines (Y/N) self-reported using AAQ	Meeting physical activity guidelines (Y/N) self-reported using AAQ
COPD Diagnostic Questionnaire (CDQ) score	COPD Diagnostic Questionnaire (CDQ) score
Dyspnoea score (mMRC)	Dyspnoea score (mMRC)
Patient Activation Measure (PAM)	Patient Activation Measure (PAM)
Daily step count (pedometer)	Daily step count (pedometer)
Smoking status	Smoking status
Self-reported exacerbations	Self-reported exacerbations
Self-reported hospital admission	Self-reported hospital admission
Self-reported emergency attendance	Self-reported emergency attendance

Physical activity will be measured in two ways. The first method will be self-reported activity levels and whether they are meeting the Australian Physical Activity and Sedentary Behaviour Guidelines [45] determined by the AAQ. The second method is the recording of daily steps from a pedometer which will be worn either around the patient’s neck or in their pocket. To assist the physiotherapist in exercise prescription, the PASOCQ [41] will also be used to determine the participant’s readiness for change. This questionnaire consists of 4 questions which places participant’s into one of the five stages of change (pre-contemplation, contemplation, preparation, action and maintenance phases).

Patient health activation will be assessed using the PAM [40] which is a 22-item measure that assesses patient knowledge, skill and confidence for self-management.

Hospital utilisation will be assessed through self-report of exacerbations, hospital admissions and emergency department attendance.

The CDQ [36] will also be assessed which is an 8-item tool developed to identify those who would benefit from spirometry testing to avoid spending time conducting tests on those unlikely to test positive. The sum score of the CDQ ranges from 0 to 38 and divides subjects into three groups of COPD likelihood: low (< 16.5), medium (16.5–19.5) and high (> 19.5).

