**Methods:**

A prospective pilot study will test the feasibility of an integrated model of care between GPs and physiotherapists to improve the diagnosis and management of people with COPD in primary care. Four general practices will be selected to work in partnership with four physiotherapists from their local health district. Patients at risk of developing COPD or those with a current diagnosis of COPD will be invited to attend a baseline assessment with the physiotherapist, including pre- and post-bronchodilator spirometry to identify new cases of COPD or confirm a current diagnosis and stage of COPD. The intervention for those with COPD will involve the physiotherapist and GP working in partnership to develop and implement a care plan involving the following tailored to patient need: referral to pulmonary rehabilitation (PR), physical activity counselling, medication review, smoking cessation, review of inhaler technique and education. Process outcomes will include the number of people invited and reviewed at the practice, the proportion with a new diagnosis of COPD, the number of patients eligible and referred to PR and the number who attended PR. Patient outcomes will include changes in symptoms, physical activity levels, smoking status and self-reported exacerbations.

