##### Sample size and feasibility

We will recruit a minimum of four general practices to the study. Based on data from a previous study [48], it is anticipated that each practice will identify 104 potentially eligible patients with a diagnosis of COPD with 50% participation and 52 patients are likely to consent to take part in the study. It is estimated that the four practices will identify a total of 1060 patients who are at risk of COPD but without a current diagnosis. Of these, 17% (180) will attend for spirometry and assessment and 18% [33] will receive a new diagnosis of COPD [12].

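### In newly diagnosed patients the COPD label and COPD education start at the baseline visit, so a before-after change in self-reported exacerbations is open to upward bias and cannot be read as an effect of the model of care

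*Protocol article*

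**What the plan says.** - **Change is the aim.** The abstract's Methods paragraph states: "Patient outcomes will include changes in symptoms, physical activity levels, smoking status and self-reported exacerbations". Under Outcome measures, data are taken at baseline, 1 month and 3 months "so the level of change in the outcomes following the intervention can be determined".
- **New cases are included.** The same section says: "Patient and process outcomes will also be collected in people with existing COPD and those with newly diagnosed COPD". Table 2 has identical rows for both groups, self-reported exacerbations among them. The text under Secondary outcomes adds: "Hospital utilisation will be assessed through self-report of exacerbations, hospital admissions and emergency department attendance".
- **New cases are unlabelled beforehand.** Sample size and feasibility describes their source as "patients who are at risk of COPD but without a current diagnosis". Under Baseline assessment, the physiotherapist uses that visit's spirometry to "determine whether the patient has a diagnosis of COPD which will be based on post-bronchodilator results".
- **Education follows the diagnosis.** Under Intervention, New cases of COPD, patients get a COPD-specific management plan, and: "Participant education booklets regarding physical activity guidelines, smoking cessation and COPD management will also be provided".
- **Design and analysis.** Methods describes a single-group before-after study. Statistical analysis plans a paired t test of baseline against 3-month questionnaire responses, two-sided at 0.05.
- **View of bias.** The Discussion concedes unblinded assessment by the treating physiotherapist, but holds that self-reporting of many outcomes lessens the effect of bias.

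**The concern.** An exacerbation is a flare-up of a disease the patient is known to have. Someone not yet diagnosed would more naturally describe the same illness as a chest infection or bronchitis. After baseline that person knows the diagnosis and has been taught about it, so the same illness is more likely to be reported as an exacerbation. The instrument, which is the patient's own recognition, changes at the moment that separates before from after.

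With no control group, a reporting shift cannot be told apart from a change in illness. The study could show an apparent worsening in the very patients it set out to find, or a real fall could be hidden. The Discussion's reassurance fails here, because for this item in this group self-report is the route by which the bias enters. The matter also carries forward: the pilot is meant to prepare a cluster randomised trial, and labelling could differ between arms there if only intervention practices look for new cases.

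**Working it through.** **1. Numbers affected (inputs from Sample size and feasibility).**
- Existing COPD: 104 × 0.50 = 52 per practice, as stated; 4 × 52 = 208.
- At-risk patients attending: 1060 × 0.17 = 180.2, stated as 180.
- New diagnoses: 180 × 0.18 = 32.4. The article prints 33 in square brackets, like a citation but where a count belongs. I take it as the count.
- Share of expected follow-up: 33 / (33 + 208) = 33/241 = 13.7%. This assumes that all 208 are confirmed on spirometry and followed; fewer would raise the share.

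**2. Size of the artefact (all inputs assumed).** The article gives no event rate, item wording or recall period. Let λ be the true number of chest illnesses per patient per 3 months, the same before and after. Let r0 and r1 be the shares reported as exacerbations before and after the label. With equal windows:
- expected change per patient = λ(r1 − r0)
- true fall that the artefact would exactly hide = 1 − r0/r1

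**3. What a paired t test would show.** Before ~ Poisson(λ·r0), after ~ Poisson(λ·r1), n = 33, two-sided 0.05, 20,000 simulations, no true change. The last three columns give the percentage of studies with a significant rise.

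| r0 / r1 | Change at λ = 0.3 | True fall hidden | λ = 0.15 | λ = 0.3 | λ = 0.5 |
|---|---|---|---|---|---|
| 1 / 1 | 0 | 0% | 2.0% | 2.4% | 2.5% |
| 0.8 / 0.9 | +0.03 | 11% | 3.1% | 4.1% | 5.3% |
| 0.5 / 0.9 | +0.12 | 44% | 9.4% | 16.0% | 26.6% |
| 0.2 / 0.9 | +0.21 | 78% | 27.7% | 52.9% | 78.1% |
| 0 / 0.9 | +0.27 | 100% | 56.2% | 94.7% | 99.8% |

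The benchmark for a false rise is about 2.5%, half of the two-sided 5%. The first row is what a symptom-based item, unaffected by the label, would give.

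**4. If both columns were pooled.** Add 208 existing patients with no reporting shift, and take λ = 0.25 and r1 = 1. For r0 = 0, 0.25 and 0.5, new cases alone give a significant rise in about 92%, 45% and 19% of studies. The pooled analysis gives about 11%, 8% and 6%.

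**5. If the windows differ.** With 12 months before baseline and 3 months after, the raw after/before ratio is 0.25 × r1/r0:
- 1/1: 0.25
- 0.8/0.9: 0.28
- 0.5/0.9: 0.45
- 0.2/0.9: 1.13

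Raw counts then fall in most of these cases. At λ = 0.25, r0 = 0.5 and r1 = 1, a significant fall appears in about 37% of studies and a significant rise in almost none.

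**The case against.** A reader might infer that exacerbations must rise in new cases through labelling alone, or that their baseline count is zero by construction. The documents do not support that, for these reasons.

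- **Wording and window are not given.** An article may leave both to the full protocol. A symptom-based item would need no label, so the artefact could be small or nil. Unequal windows could reverse the direction, as step 5 shows. This stands, and the conclusion is conditional on it.
- **The test is not clearly tied to this item.** The t test is for questionnaire responses, and the questionnaires listed under Baseline assessment include no exacerbation item. Nor does the article say that new cases are tested alone. This stands: the probabilities above are illustrations and do not forecast this study's result.
- **Admissions and emergency attendances.** A reader might extend the point to these. As printed in Table 2 they are not restricted to COPD and need no label, so the point does not reach them.
- **The columns do not split exactly by label.** The Existing COPD criteria admit patients who take COPD medication without a recorded diagnosis. This stands as a caveat to any analysis by column.
- **Low consequence.** This is one of ten patient outcomes, and the success targets for case-finding, referral and attendance do not use it. This too stands.

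None of this removes the core. The article itself fixes a before-after change in a label-dependent outcome, in a group defined by acquiring the label at baseline, without a control group. A baseline recall question about exacerbations would not by itself cure that, because the label still changes at that visit.

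**Conclusion.** The concern holds in conditional form. If the item depends on the patient recognising an exacerbation, and the recall windows are equal, the change in new cases is open to upward bias from labelling and education. It should not be read as an effect of the model of care. The Discussion's statement that self-report lessens bias does not hold for this item in this group.

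The size cannot be fixed from the article. Across the assumed rates and reporting shares, the chance of a false significant rise in 33 new cases runs from its nominal level to near certainty. Moderate under-recognition before baseline (50% against 90% after) gives about 9% to 27%, and pooling with existing cases would dilute the effect. The reach is limited: one secondary outcome in about 14% of expected follow-up patients. No sample-size figure or feasibility criterion depends on it.

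**What to change.** For new cases, replace the exacerbation row of Table 2 with a label-neutral item, such as chest illnesses that led to an unscheduled visit or a course of treatment. Ask it in the same words and over the same recall window at baseline and 3 months.

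If the exacerbation item is kept, report it in new cases only as a descriptive 3-month count, apart from the Existing COPD column, with no before-after change or test. Note there that some patients in the existing group may also lack a recorded diagnosis.

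In either case, qualify the Discussion's sentence on self-report: for exacerbations in newly diagnosed patients, the diagnosis and education may themselves alter what is reported.

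The cost is one reworded item, one table row and one sentence, with no extra visits, staff or patients. The small downside is that a neutral item is less specific to COPD.
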